**Figure 1 fig1:**
[figure not shown]
Study design (randomized controlled trials) and assessment time points (consort chart).

### Study population

This single-center randomized controlled trial will recruit patients with pDoC due to ICH, specifically those in the chronic phase (3–12 months post-injury). The study will be conducted at the Department of Rehabilitation, Guangdong Sanjiu Brain Hospital.

#### Inclusion criteria

(1) Age: 18–65 years; (2) Diagnosed with DOC (vegetative state or minimally conscious state) according to the Coma Recovery Scale-Revised (CRS-R) (24); (3) Time since ICH: 3–12 months, which represents the chronic phase for hemorrhagic etiology; (4) Stable vital signs without need for mechanical ventilation; (5) No significant changes in CRS-R total score (defined as a change of ≤2 points) for at least 2 weeks prior to enrollment; (6) No skull defects or metal implants in the brain that could interfere with tDCS; (7) Written informed consent obtained from the legal representative.

#### Exclusion criteria

(1) Severe complications that may affect assessment or treatment, such as severe spasticity, joint contractures, or pressure ulcers; (2) History of epilepsy or seizures within the past 3 months; (3) Pregnancy or lactation; (4) Participation in other interventional studies within the past 30 days; (5) Contraindications for tDCS or MNS, such as skin lesions at stimulation sites, implanted electronic devices, or allergies to electrode materials; (6) Current use of medications that may significantly alter cortical excitability (e.g., high-dose benzodiazepines, antiepileptic drugs) (13); (7) Neuroimaging evidence of severe brain atrophy (defined as a global cortical atrophy scale score >2 on the 0–3 Pasquier scale, or ventricular-brain ratio >0.25 on axial MRI slices) or hydrocephalus (defined as Evans’ index >0.30 on axial CT or MRI slices). These assessments will be conducted by two independent neuroradiologists with experience in interpreting neuroimaging in patients with disorders of consciousness; (8) History of neurodegenerative diseases or psychiatric disorders; (9) Inability to complete the full course of treatment or follow-up assessments.

### Sample size

Sample size calculation was performed using the Coma Recovery Scale-Revised (CRS-R) score as the primary outcome measure. We employed a one-way analysis of variance (ANOVA) model to determine the required sample size (25). Calculations were conducted using G*Power software (version 3.1.9.7, University of Düsseldorf, Germany) (26).

Based on previous similar studies (14, 27), we assumed a clinically significant difference of 4 points in CRS-R scores between the treatment and control groups. This threshold is based on previous research by Estraneo et al. (24), which demonstrated that a 4-point change in CRS-R score is associated with meaningful transitions between diagnostic categories and correlates with clinically observable improvements in patient responsiveness and function, with a standard deviation of 7.3 points. The significance level (*α*) was set at 0.05, and the power (1-*β*) at 0.8, which are commonly used parameters in clinical trials (28).

For a 3 × 6 mixed repeated measures ANOVA (one 3-level between-subjects factor and one 6-level within-subject factor), G*Power calculated a required sample size of 22 participants per group to detect a medium effect size (*f* = 0.25) with 80% power at a 5% significance level, considering correlations among repeated measures of 0.5 and a nonsphericity correction of 0.75. To account for potential dropouts and loss to follow-up, we increased the sample size by 20% (19, 29). Consequently, the final sample size was determined to be 27 participants per group, totaling 81 participants for the three-group study design.

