### Outcome measures

#### Primary outcome measure

The primary outcome measure is the change in total score on the Coma Recovery Scale-Revised (CRS-R) from baseline to post-treatment (24). The CRS-R is the gold standard for assessing patients with disorders of consciousness and comprises six subscales: auditory, visual, motor, oromotor, communication, and arousal, with a total score range of 0–23 (32). CRS-R assessments will be conducted by trained evaluators at baseline, after 4 weeks of treatment, and at 2 weeks, 4 weeks, 12 weeks, and 24 weeks post-intervention. To ensure consistency and accuracy, all evaluators will undergo standardized training and pass a video scoring test to ensure inter-rater reliability (ICC > 0.8) (24).

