All statistical analyses will be conducted using R software (version 4.1.0 or higher), with a significance level set at *α* = 0.05 (two-sided). To control for Type I error inflation due to multiple comparisons, Bonferroni correction will be applied to adjust *p*-values for secondary outcomes (43).

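### The 80% power claim is not shown for the 4-point difference on the declared primary outcome; 22 per group answers a different question

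*Protocol article*

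**What the plan says.** The Sample size section names two models. It opens with "We employed a one-way analysis of variance (ANOVA) model to determine the required sample size". It then states that "we assumed a clinically significant difference of 4 points in CRS-R scores between the treatment and control groups", gives an SD of 7.3 points, and sets alpha at 0.05 and power at 0.8. The next paragraph changes to a 3 × 6 mixed repeated-measures ANOVA and reports that "G*Power calculated a required sample size of 22 participants per group to detect a medium effect size". That effect is f = 0.25, and the power claimed for it is 80%. Two further inputs are a within-patient correlation of 0.5 and an ε of 0.75. The 22 is raised by 20% to 27 per group, 81 in total.

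Under Primary outcome measure: "The primary outcome measure is the change in total score on the Coma Recovery Scale-Revised (CRS-R) from baseline to post-treatment". Statistical methods plans a 3 × 6 repeated-measures ANCOVA with corrected post-hoc group comparisons. Its covariate item says that baseline values of the outcome will routinely be adjusted for. The abstract gives an enrolment of 138 alongside three groups of 27.

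**The concern.** The section places a clinical target (4 points, SD 7.3) and an 80% power figure next to each other, but the power figure belongs to f = 0.25 in a repeated-measures model. The text does not connect f = 0.25 to 4 points, does not say which effect is tested (group, time or their interaction), and does not say which of the software's effect-size conventions was used. The declared primary outcome is one change, compared between groups.

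If 22 per group does not give 80% power for that comparison, the published statement promises more than the design delivers. A null result could then be taken as evidence against a 4-point benefit from an adequately powered trial, when the trial may have had about an even chance of detecting it.

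**Working it through.** **Inputs.** From Sample size: k = 3 groups, m = 6 visits, f = 0.25, correlation ρ = 0.5, ε = 0.75, difference 4, SD 7.3, alpha 0.05. Statistical methods makes the tests two-sided. Power is from the noncentral F or t distribution; N = 66 is 3 × 22.

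**1. Reproducing the plan's 22.** For the group-by-time interaction under the Cohen (1988) option:
- λ = f²·N·(m−1)·ε = 0.0625 × 66 × 5 × 0.75 = 15.47
- df = (k−1)(m−1)ε = 7.5 and (N−k)(m−1)ε = 236.25
- power 0.810; at N = 63 (21 per group) it is 0.787

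So 22 per group is reproduced exactly. This formula contains no ρ. The SPSS-type option, with N−k in place of N in λ, also omits ρ and gives 23.

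**2. Using the stated ρ = 0.5 (default option), f = 0.25.**
- Group factor: λ = f²·N·m/(1+(m−1)ρ) = 0.0625 × 66 × 6/3.5 = 7.07; power 0.64 at N = 66; 80% needs N = 93, or 31 per group.
- Interaction: λ = f²·N·m·ε/(1−ρ) = 0.0625 × 66 × 6 × 0.75/0.5 = 37.1; power 0.998 at N = 66; 80% needs about 10 per group.

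Neither gives 22.

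**3. The one-way ANOVA named first.** With means 4, 0, 0, f = (4√2/3)/7.3 = 0.258, and λ = N·f².
- f = 0.25: power 0.41 at N = 66; 80% needs 159, or 53 per group.
- f = 0.258: power 0.43 at N = 66; 80% needs 150, or 50 per group.

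**4. What 4 points mean as an interaction.** Suppose the combination gains 4 points at all five post-baseline visits and the controls gain none.
- Interaction mean square = (2/9) × 16 × (5/6) × (1/6) = 0.494
- f = √0.494/7.3 = 0.096
- λ = 0.0963² × 66 × 6 × 0.75/0.5 = 5.50; power about 0.33

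Thus 0.25 is close to the single-visit f (0.258), but the route that gives 22 uses it as an interaction f.

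**5. Power for the declared primary outcome.** I assume that 7.3 is the SD of the score. About 22 per group are evaluable (27 × 0.8 = 21.6). The comparison is the combination against one control at week 4. Unadjusted, d = 4/7.3 = 0.548. Adjusted, the residual SD is 7.3√(1−ρ²), where ρ is now the baseline-to-week-4 correlation. The values 0.7 and 0.8 are my assumptions; 0.5 is the protocol's.

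| Analysis | Residual SD | Power, alpha 0.05 | Power, alpha 0.025 (two comparisons) |
|---|---|---|---|
| Unadjusted | 7.30 | 43% | 32% |
| Adjusted, ρ = 0.5 | 6.32 | 54% | 42% |
| Adjusted, ρ = 0.7 | 5.21 | 70% | 59% |
| Adjusted, ρ = 0.8 | 4.38 | 84% | 76% |

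The unadjusted t-test needs 54 per group for 80% power. With all 27 per group evaluable it has 51%.

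**6. Detectable difference at 22 per group, 80% power, no multiplicity correction.** Unadjusted it is 6.3 points, or 6.3/7.3 = 0.87 residual SDs. Multiplying by the adjusted SDs gives about 5.5, 4.5 and 3.8 points.

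**7. If 7.3 is instead the SD of the change.** The adjusted residual SD is 7.3√((1+ρ)/2) = 6.3, 6.7 or 6.9 at the same three correlations. All lie between 6.32 and 7.30, so uncorrected power stays between about 43% and 54%.

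**The case against.** The strongest reply is that 22 is a legitimate software result. That is correct: a reader might infer that it is an arithmetic error, but the documents do not support this, because a standard option returns it exactly. What remains is that the section names neither the effect nor the option, and says that a correlation was considered which plays no part in that option.

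A second reply is that 43% is the power of an unadjusted single-visit test, while the protocol plans a repeated-measures analysis with routine baseline adjustment. This also has force. A reader might infer that the trial simply has 41–43% power; the documents do not support that as an unconditional figure. The two-week CRS-R stability criterion means that a high baseline correlation cannot be excluded, and at 0.8 the adjusted single-visit test reaches 84% before any multiplicity correction. A baseline-adjusted mean of the five post-baseline visits would have about 85–87% at ρ = 0.5. However, neither the primary outcome definition nor the analysis section specifies that mean as the deciding comparison, and the only correlation in the protocol is 0.5.

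A third reply is that 138 patients may be intended. At 46 per group the unadjusted power for 4 points would be about 74%, so the conflict in enrolment bears directly on the power statement.

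**Conclusion.** The power statement is wrong as written. The calculation behind 22 per group does not support 80% power for a 4-point difference in the change from baseline to post-treatment. At the protocol's own correlation of 0.5, the baseline-adjusted week-4 comparison has about 54% power at 22 evaluable per group, or 42% with Bonferroni for two comparisons.

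These figures rest on 7.3 being the SD of the score and on a pairwise week-4 comparison deciding the trial. The Bonferroni choice is illustrative, since the protocol promises a correction for post-hoc group comparisons without naming it there. Among the correlations tried, only 0.8 without a multiplicity correction takes the single-visit test above 80%. The conclusion is that 80% is not shown, not that it is unattainable under every analysis.

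**What to change.** In Sample size, delete the justification by 22 per group, f = 0.25 and 80% power, along with the one-way ANOVA sentence if that model will not be used. Then:

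- Name the test and effect that decide the primary outcome. The natural choice is the baseline-adjusted week-4 comparison of the combination with each control.
- State whether 7.3 is the SD of the score or of the change.
- Restate power for 4 points, or the detectable difference, for 27 randomised and about 22 evaluable per group, over a range of baseline correlations and with the multiplicity correction that will be used. The table above can serve as a starting point if 7.3 is the SD of the score.
- Reconcile the abstract's 138 with the 81 in Sample size, and base the restated power on the number that stands.

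Correcting the statement needs no extra patients. The cost is a rewritten section and a less favourable stated power.

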### Experimental group intervention

The experimental group (tDCS+MNS group) will receive tDCS combined with MNS. tDCS will be administered using a Starstim tDCS stimulator (Neuroelectrics, Barcelona, Spain). The anode electrode (5 × 7 cm) will be placed over the left dorsolateral prefrontal cortex (F3 position according to the international 10–20 system), and the cathode electrode (5 × 7 cm) will be placed over the right supraorbital area (Fp2 position). Stimulation will be delivered at 2 mA for 20 min, with ramp-up and ramp-down periods of 30 s each, once daily for 5 consecutive days per week, for 4 weeks. MNS will be administered using a Digitimer DS7A constant current stimulator (Digitimer Ltd., Hertfordshire, UK). Electrodes will be placed on the right median nerve (2 cm proximal to the wrist crease), with intensity set at 300% of the motor threshold, frequency at 10 Hz, pulse width at 1 ms, for a total duration of 120 min. The MNS will begin 10 min before tDCS starts and continue for 90 min after tDCS ends, ensuring a 20-min overlap of both stimulations (30). The combined tDCS and MNS stimulation protocol is shown in Figure 2, which details the stimulation parameters and timing sequence.

**Figure 2 fig2:**
[figure not shown]
Combined tDCS and MNS protocol for patients with pDoC.

### Control group interventions

Control Group 1 (Sham tDCS+MNS group) will receive sham tDCS combined with MNS treatment. Sham tDCS will ramp up to 2 mA over 30 s, then ramp down to 0 over 30 s, and remain off thereafter (31). MNS parameters will be identical to the experimental group.

Control Group 2 (tDCS+Sham MNS group) will receive sham MNS combined with tDCS treatment. tDCS parameters will be identical to the experimental group, but MNS intensity will be set at 50% of the sensory threshold, insufficient to elicit muscle contraction (20).

### Permitted/prohibited concomitant interventions

All patients will continue to receive standard rehabilitation therapy, including physical and occupational therapy. Medications necessary for maintaining stable vital signs, such as antihypertensive and antiepileptic drugs, are permitted. The use of drugs that may significantly affect consciousness levels or brain excitability, such as high-dose sedatives or anesthetics, is prohibited (22). If such medications are required, their use will be documented and considered in the analysis. Participation in other experimental treatments or clinical trials is prohibited.

### Outcome measures

#### Primary outcome measure

The primary outcome measure is the change in total score on the Coma Recovery Scale-Revised (CRS-R) from baseline to post-treatment (24). The CRS-R is the gold standard for assessing patients with disorders of consciousness and comprises six subscales: auditory, visual, motor, oromotor, communication, and arousal, with a total score range of 0–23 (32). CRS-R assessments will be conducted by trained evaluators at baseline, after 4 weeks of treatment, and at 2 weeks, 4 weeks, 12 weeks, and 24 weeks post-intervention. To ensure consistency and accuracy, all evaluators will undergo standardized training and pass a video scoring test to ensure inter-rater reliability (ICC > 0.8) (24).

#### Secondary outcome measures

(1) Functional Near-Infrared Spectroscopy (fNIRS): To assess cortical hemodynamic changes, reflecting brain functional connectivity (33). Measurements will be taken at baseline and after 4 weeks of treatment.

(2) Electroencephalography (EEG): To evaluate changes in brain electrical activity, including power spectral analysis and functional connectivity analysis (34). Measurements will be taken at baseline and after 4 weeks of treatment.

(3) Event-Related Potentials (ERPs): To assess cognitive processing abilities, focusing on the P300 component (35). Measurements will be taken at baseline and after 4 weeks of treatment.

(4) Glasgow Outcome Scale-Extended (GOS-E): To evaluate overall functional outcomes (36). Assessments will be conducted at baseline, 4 weeks, and 12 weeks follow-up.

(5) Functional Magnetic Resonance Imaging (fMRI): To be assessed at baseline and 24 weeks follow-up.

(6) Adverse Events: All treatment-related adverse events will be recorded, including type, severity, and duration. Continuous monitoring will be conducted during each treatment session and throughout the follow-up period.

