This study employs a triple-blind design, where patients, outcome assessors, and data analysts will be blinded to treatment allocation. Patients, outcome assessors, and data analysts will be blinded to treatment allocation. To achieve this, we will adopt the following strategies: (1) All patients will receive identical electrode placement and stimulation duration, regardless of real or sham stimulation. (2) tDCS and MNS devices will be pre-programmed to provide either real or sham stimulation. These devices will be identical in appearance and operated by technicians not involved in patient assessment. (3) Sham stimulation will deliver a brief current for the initial 30 s, mimicking the sensation of real stimulation, before gradually ramping down to zero. This sham tDCS protocol has been validated in previous studies with both healthy participants and patients with disorders of consciousness, showing that participants cannot reliably distinguish between real and sham stimulation (20). (4) All research personnel will receive standardized training to ensure consistency in treatment and assessment procedures. To maintain blinding, we will implement the following measures: (1) All research personnel and participants will be instructed not to discuss treatment details during the study. (2) The effectiveness of blinding will be regularly assessed by asking assessors to guess the type of treatment they evaluated. For patients who regain communication ability during the study (emerging from MCS), we will also ask them to guess which treatment they received, but this will not be possible for patients who remain in pDoC throughout the study. (3) During the data analysis phase, treatment groups will be coded (e.g., A, B, C) until all analyses are completed. Unblinding will only occur in the event of serious adverse events or when patient safety considerations necessitate it. The unblinding procedure will be executed by an independent safety monitoring committee not involved in daily patient management.

Patient recruitment is scheduled to begin on October 1, 2024, with all follow-ups expected to be completed by September 31, 2025. The primary outcome measure (CRS-R scores) will be assessed at baseline, after 4 weeks of treatment, and at 2 weeks, 4 weeks, 12 weeks, and 24 weeks post-intervention (24).

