#### Study safety

Based on previous research, transcranial direct current stimulation and median nerve stimulation are considered relatively safe, non-invasive techniques (16). However, we will closely monitor potential adverse events, including but not limited to: (1) mild discomfort, redness, or itching at the stimulation site; (2) transient headache or dizziness; (3) nausea; (4) fatigue. To address these potential adverse events, we have developed a detailed response plan: (1) All research personnel will receive training in adverse event identification and management. (2) Given that patients with prolonged disorders of consciousness (pDoC) cannot reliably self-report subjective adverse events, a comprehensive monitoring approach has been implemented, including systematic observation of objective signs (skin reactions, autonomic changes such as heart rate, blood pressure, and sweating, facial expressions, and behavioral responses); physiological parameter monitoring (temperature, blood pressure, and heart rate before and after each session); neurophysiological indicators (EEG changes during treatment and follow-up that may indicate discomfort or adverse responses); caregiver reports (detailed inquiries to family members and caregivers about any unusual behaviors or responses); and clinical judgment (comprehensive assessment by experienced clinicians familiar with detecting subtle signs of discomfort in non-communicative patients). (3) Detailed assessments using the above methods will be conducted before and after each treatment session and at all follow-up visits. (4) Any identified adverse events will be documented and evaluated by a physician not involved in the direct treatment delivery. (5) For adverse events management, we will implement a standardized classification system based on the Common Terminology Criteria for Adverse Events (CTCAE v5.0). All adverse events will be graded on a 5-point scale (1: mild; 2: moderate; 3: severe; 4: life-threatening; 5: death-related) and systematically documented in a dedicated adverse event log. Events of grade 3 or higher will be reported to the ethics committee within 24 h.

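### The adverse-event outcome covers only treatment-related events, while the safety section and Table 1 cover all adverse events; restate the outcome as all events by arm

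*Protocol article*

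**What the plan says.** In the protocol article, Secondary outcome measures, item (6), reads: "All treatment-related adverse events will be recorded, including type, severity, and duration". It adds that monitoring runs through each treatment session and the follow-up period.

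The Study safety section is wider. It states: "Any identified adverse events will be documented and evaluated by a physician not involved in the direct treatment delivery". It then says "All adverse events will be graded on a 5-point scale", under CTCAE v5.0, and that events are "systematically documented in a dedicated adverse event log". None of these statements refers to relatedness. The adverse-event row of Table 1, marked from Week 4 to Week 28, is likewise unrestricted.

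Study safety also acknowledges that "patients with prolonged disorders of consciousness (pDoC) cannot reliably self-report subjective adverse events". Detection therefore relies on observed signs, physiological measurements, EEG, caregiver reports and "clinical judgment (comprehensive assessment by experienced clinicians familiar with detecting subtle signs of discomfort in non-communicative patients)".

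On blinding, Study design says that "patients, outcome assessors, and data analysts will be blinded to treatment allocation". The physician who evaluates adverse events is not named among these roles. The Statistical methods section describes no analysis of adverse events.

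**The concern.** An outcome definition tells the analyst which events to count. Here the definition in the outcome list is the narrower of two in the same article. An analysis that follows it would pass each event through a causality judgement before it reaches the safety table.

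In a randomised trial that filter is unnecessary for comparing arms, and it carries a risk. The judgement is made after allocation. If it is imperfect, a real difference between arms can be diluted. If it is influenced by apparent allocation, a difference can be created. Safety is one of the trial's stated aims, so the choice of events bears directly on one of its conclusions.

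**Working it through.** The plan gives no adverse-event rate, no safety power and no figure to reproduce, so no arithmetic applies. The check is a comparison of the text.

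1. **Which events are in scope.**
   - Outcome (6): treatment-related events, with type, severity and duration.
   - Study safety: any identified event is documented and evaluated; all are graded and logged.
   - Table 1: adverse events, without qualification.

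   Two of the three places cover all events. The one that defines the outcome covers a subset. An event judged unrelated is in the log under Study safety but outside the outcome under item (6).

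2. **How relatedness is decided.** The article gives no rule. Nor does item (6) say whether an event must be related to tDCS, to MNS or to either. This matters because every arm receives at least one real stimulation: both in the combination arm, MNS in the sham-tDCS arm, and tDCS in the sham-MNS arm.

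3. **On what evidence.** The patients cannot reliably describe subjective symptoms, so detection is already indirect. Attribution adds a second inference to the first.

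4. **By whom.** The evaluating physician is separate from treatment delivery, which helps, but is not listed among the blinded roles. Real MNS is given with "intensity set at 300% of the motor threshold", whereas Control group interventions sets sham MNS at 50% of the sensory threshold, too low to produce muscle contraction. Anyone who sees a session could therefore have a clue to MNS allocation. Whether the evaluating physician sees sessions is not stated.

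5. **Whether the wider data would exist.** They would. Study safety already requires all events to be documented, graded and logged, so an all-event summary needs no new data collection.

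6. **Where else relatedness is used.** It is one of the criteria for discontinuing treatment after a grade 3 or higher event. That use is separate from what is counted as the outcome and is not in question here.

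**The case against.** The strongest reply is that item (6) is a statement about recording and not an analysis endpoint. No section says that only related events will be tabulated or compared between arms, and the content of safety tables is normally left to an analysis plan, which is not shown. Study safety, the more detailed text, already secures capture of all events. On this view a single adjective needs tidying.

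Much of this stands, and it rules out several stronger readings that a reader might reach:

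- **That unrelated events will be lost.** The log in Study safety covers them.
- **That a filtered between-arm comparison is planned.** No adverse-event analysis is described. The comparison is implied only because adverse events are a listed secondary outcome of a randomised trial.
- **That attribution will be biased.** The physician's blinding is unstated, which does not show that the physician is unblinded. No text supports a claim that particular events would readily be dismissed as unrelated.
- **That an all-event comparison would show everything the stimulation causes.** Each arm has at least one real stimulation, so contrasts with the combination arm show only what one component adds to the other. Harm common to all arms would not appear, and relatedness assessment keeps a use for that reason.
- **That the trial plans to conclude from this outcome that the treatment is very safe.** The favourable safety statement in the Introduction is background on the techniques.

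The reply does not remove the contradiction. Item (6) stands in the list of outcomes, and an analyst who follows it as written would report the subset. This is not detail left to another document: the article itself fixes two incompatible scopes.

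**Conclusion.** The point holds as an inconsistency in the definition of a declared secondary outcome, and it should be corrected before the data are analysed. Followed literally, outcome (6) makes the reported safety result depend on unspecified relatedness judgements in patients who cannot reliably self-report. That consequence is conditional on the narrower wording governing the analysis, which the article neither confirms nor excludes.

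No numerical size can be given. It would require the event rate in each arm and the share of caused and background events labelled as related, and the article supplies neither. Any worked percentage would be invention.

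**What to change.** Reconcile the two sections by restating outcome (6) as all adverse events and all serious adverse events, regardless of relatedness, from first stimulation to Week 28. Summarise them by randomised arm, as patients with at least one event and by CTCAE grade.

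Keep relatedness as a recorded attribute and report related events in a supplementary table. State whether the physician who judges relatedness is blinded to allocation, and to which component (tDCS, MNS or either) the judgement refers.

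The cost is rewording and one extra table. The data are already required by Study safety, and no clinical rule changes.
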